### 8.3. Subjects Lost to Follow-up

A subject will be considered lost to follow-up if he or she repeatedly fails to return for scheduled visits and is unable to be contacted by the study site. Site personnel are expected to make diligent attempts to contact subjects who fail to return for a scheduled visit or were otherwise unable to be followed up by the site.

## 9. Study Assessments and Procedures

Section 2 lists the Schedule of Activities, detailing the study procedures and their timing (including tolerance limits for timing).

Appendix 2 lists the laboratory tests that will be performed for this study.

Appendix 5 provides a summary of the maximum number and volume of invasive samples, for all sampling, during the study.

Unless otherwise stated in subsections below, all samples collected for specified laboratory tests will be destroyed within 60 days of receipt of confirmed test results. Certain samples may be retained for a longer period, if necessary, to comply with applicable laws, regulations, or laboratory certification standards.

### 9.1. Efficacy Assessments

Pharmacodynamic assessments are described in Section 9.6.

### 9.2. Adverse Events

Investigators are responsible for monitoring the safety of subjects who have entered this study and for alerting Lilly or its designee to any event that seems unusual, even if this event may be considered an unanticipated benefit to the subject.

The investigator is responsible for the appropriate medical care of subjects during the study.

Investigators must document their review of each laboratory safety report.

The investigator remains responsible for following, through an appropriate health care option, AEs that are serious or otherwise medically important, considered related to the investigational product or the study, or that caused the subject to discontinue the investigational product before completing the study. The subject should be followed up until the event resolves, stabilizes with appropriate diagnostic evaluation, or is reasonably explained. The frequency of follow-up evaluations of the AE is left to the discretion of the investigator.

The investigator will record all relevant AE and SAE information in the eCRF. After the ICF is signed, study site personnel will record, via eCRF, the occurrence and nature of each subject's preexisting conditions, including clinically significant signs and symptoms of the disease under treatment in the study. Additionally, site personnel will record any change in the condition(s) and the occurrence and nature of any AEs.

The investigator will interpret and document whether or not an AE has a reasonable possibility of being related to study treatment or a study procedure, taking into account the disease, concomitant treatment, or pathologies.

A "reasonable possibility" means that there is a potential cause and effect relationship between the investigational product and/or study procedure and the AE.

Planned surgeries should not be reported as AEs, unless the underlying medical condition has worsened during the course of the study.

If a subject's investigational product is discontinued as a result of an AE, study site personnel must report this to Lilly or its designee via eCRF.

### **9.2.1. Serious Adverse Events**

An SAE is any AE from this study that results in 1 of the following:

- death
- initial or prolonged inpatient hospitalization
- a life-threatening experience (that is, immediate risk of dying)
- persistent or significant disability/incapacity
- congenital anomaly/birth defect
- important medical events that may not be immediately life-threatening or result in death or hospitalization but may jeopardize the subject or may require intervention to prevent 1 of the other outcomes listed in the definition above.

Study site personnel must alert the Lilly CRP/CP, or its designee, of any SAE as soon as practically possible.

Additionally, study site personnel must alert Lilly Global Patient Safety, or its designee, of any SAE within 24 hours of investigator awareness of the event via a sponsor-approved method. If alerts are issued via telephone, they are to be immediately followed up with official notification on study-specific SAE forms. This 24-hour notification requirement refers to the initial SAE information and all follow-up SAE information.

Although all AEs are recorded in the eCRF after signing informed consent, SAE reporting to the sponsor begins after the subject has signed informed consent and has received investigational product. However, if an SAE occurs after signing informed consent, but prior to receiving investigational product, AND is considered reasonably possibly related to a study procedure then it MUST be reported.

Investigators are not obligated to actively seek AEs or SAEs in subjects once they have discontinued from and/or completed the study (the subject summary case report form has been completed). However, if the investigator learns of any SAE, including a death, at any time after a subject has been discharged from the study, and he/she considers the event reasonably possibly related to the study treatment or study participation, the investigator must promptly notify Lilly.

Pregnancy (maternal or paternal exposure to investigational product) does not meet the definition of an AE. However, to fulfill regulatory requirements any pregnancy should be reported following the SAE process to collect data on the outcome for both mother and fetus.

**9.2.1.1. Suspected Unexpected Serious Adverse Reactions**

Suspected unexpected serious adverse reactions (SUSARs) are serious events that are not listed in the IB and that the investigator reports as related to investigational product or procedure. Lilly has procedures that will be followed for the recording and expedited reporting of SUSARs that are consistent with global regulations and the associated detailed guidances.

**9.2.2. Complaint Handling**

Lilly collects product complaints on investigational products and drug delivery systems used in clinical trials to ensure the safety of study participants, monitor quality, and to facilitate process and product improvements.

Subjects should be instructed to contact the investigator as soon as possible if they have a complaint or problem with the investigational product so that the situation can be assessed.

**9.3. Treatment of Overdose**

For the purposes of this study, an overdose of LY3475766 is considered any dose higher than the dose assigned through randomization. The treatment for overdose is supportive care.

Refer to the IB for LY3475766.

**9.4. Safety****9.4.1. Laboratory Tests**

For each subject, laboratory tests detailed in [Appendix 2](#) should be conducted according to the Schedule of Activities (Section [2](#)).

With the exception of test results that may unblind the study, Lilly or its designee will provide the investigator with the results of safety laboratory tests analyzed by a central vendor, if a central vendor is used for the study.

**9.4.2. Vital Signs**

For each subject, vital sign measurements should be conducted according to the Schedule of Activities (Section [2](#)).

Blood pressure and pulse rate should be measured after the subject has been sitting for at least 5 minutes comfortably in a quiet environment, in a chair with back support, legs uncrossed, feet touching the floor, and arm resting at heart level.

Unscheduled orthostatic vital signs should be assessed, if possible, during any AE of dizziness or posture-induced symptoms. If orthostatic measurements are required, subjects should be supine for at least 5 minutes and stand for at least 2 minutes. If the subject feels unable to stand, supine vital signs only will be recorded. Additional vital signs may be measured if considered necessary by the investigator.

Body temperature will be measured, as specified in the Schedule of Activities (Section [2](#)), and as clinically indicated.

The AOBPM will be performed according to the Schedule of Activities (Section 2). Site investigative personnel should be trained on the correct positioning of the AOBPM device, use of correct cuff size, and monitor calibration prior to the start of the study.

The subject should avoid eating, drinking (except water), or smoking 30 minutes before AOBPM. The subject is seated comfortably in a chair with back support, legs uncrossed, feet touching the floor, and arm resting at heart level.

The AOBPM will be performed by CRU staff that have appropriate training in collecting BP. After resting for 5 minutes, the BP measurements will occur.

Four BP readings are recorded 1 minute apart; the latter 3 are averaged, and the first reading is discarded. The average of the 3 BP measurements is considered for analysis.

The AOBPM done after Day 1 should be done at approximately the same time of day as predose and done under similar conditions.

#### **9.4.3. Telemetry**

For each subject, single-lead ECG telemetry will be performed during each stay at the CRU involving at least 1 night (see Schedule of Activities in Section 2). The telemetry system has standard alarms to alert the clinical staff to any detected abnormalities, for example, cardiac arrhythmias, prolongation of QT, during which additional 12-lead ECGs may be obtained at the investigator's discretion. These may also be performed in the event of technical or logistical impediments to the use of telemetry. In order to bathe, subjects may remove the telemetry device for up to 1 hour, which should be documented.

#### **9.4.4. Electrocardiograms**

For each subject, a single 12-lead digital ECG will be collected according to the Schedule of Activities (Section 2). Electrocardiograms must be recorded before collecting any blood samples. Subjects must be supine for approximately 5 to 10 minutes before ECG collection and remain supine but awake during ECG collection. Electrocardiograms may be obtained at additional times, when deemed clinically necessary. All ECGs recorded should be stored at the investigational site.

Electrocardiograms will be interpreted by a qualified physician at the site as soon after the time of ECG collection as possible, and ideally while the subject is still present, to determine whether the subject meets entry criteria at the relevant visit(s) and for immediate subject management, should any clinically relevant findings be identified. The screening ECG may be initially reviewed by a qualified non-physician designated by the investigator but must be reviewed by a physician to confirm eligibility before randomization.

Any clinically significant findings from ECGs that result in a diagnosis and that occur after the subject receives the first dose of the investigational product should be reported to Lilly, or its designee, as an AE via eCRF.

If a clinically significant finding is identified (including, but not limited to, changes in QT/QT interval corrected for heart rate [QTc] interval from baseline) after enrollment, the investigator will determine if the subject can continue in the study. The investigator, or qualified designee, is responsible for determining if any change in subject management is needed, and must document his/her review of the ECG printed at the time of collection.

Collection of ECG replicates at a particular time point will be permitted to ensure high-quality records.

Starting at Day 1, all digital ECGs (scheduled and unscheduled) will be electronically transmitted to a central ECG laboratory designated by Lilly. The central ECG laboratory will perform a basic quality control check (for example, demographics and study details) and then store the ECGs in a database. At a future time, the stored ECG data may be overread at the central ECG laboratory for further evaluation of machine-read measurements or to meet regulatory requirements.

The machine-read ECG intervals and heart rate may be used for data analysis and report writing purposes unless a cardiologist overread of the ECGs is conducted prior to completion of the final study report (in which case the overread data would be used).

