**Table GZEA.1. Objectives and Endpoints**

| Objectives                                                                                                                                                                                                                                                                                               | Endpoints                                                                                                                                                                                           |
|----------------------------------------------------------------------------------------------------------------------------------------------------------------------------------------------------------------------------------------------------------------------------------------------------------|-----------------------------------------------------------------------------------------------------------------------------------------------------------------------------------------------------|
| Primary 
 
To assess the safety and tolerability of single IV and SC doses of LY3475766 in dyslipidemic but otherwise healthy subjects.
 
                                                                                                     | 
 
Incidence of AEs and SAEs
 
Clinically significant changes in vital signs, safety laboratory parameters, and ECGs
 
                          |
| Secondary 
 
To characterize the PK of LY3475766 following single doses in dyslipidemic but otherwise healthy subjects.
 
To characterize the PD of LY3475766 following single doses in dyslipidemic but otherwise healthy subjects.
 
 | 
 
AUC, <math>C_{\max}</math>, and <math>t_{\max}</math>
 
Absolute and percent change from baseline in fasting levels of TG, LDL-C, and apoB
 
 |

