#### **10.3.1.2. Statistical Evaluation of Safety**

Safety parameters that will be assessed include safety laboratory parameters, vital signs, and ECG parameters. The parameters will be listed and summarized using standard descriptive statistics.

The relationship between systolic BP, diastolic BP, and heart rate from AOBPM and the PK concentration will be evaluated through a longitudinal linear model with independent variables of PK concentration as a continuous variable and time relative to the first dose time as a categorical variable. A compound-symmetry variance-covariance structure will be used to model the within-subject correlation.

The mean systolic BP, diastolic BP, and heart rate by dose will be plotted against time. The maximum value (for each subject) within the 9 weeks after the first dose will be summarized and compared between dose groups using a linear model with dose as a factor and baseline mean value of the corresponding analysis variable as a covariate.

Additional analysis will be performed if warranted upon review of the data.

Baseline for safety parameters will be defined as the last evaluable value before the first dose.

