| AE                                 | adverse event: Any untoward medical occurrence in a patient or clinical investigation subject administered a pharmaceutical product that does not necessarily have a causal relationship with this treatment. An AE can therefore be any unfavorable and unintended sign (including an abnormal laboratory finding), symptom, or disease temporally associated with the use of a medicinal (investigational) product, whether or not related to the medicinal (investigational) product.                                                                                                                                                                                                   |
| ALP                                | alkaline phosphatase                                                                                                                                                                                                                                                                                                                                                                                                                                                                                                                                                                                                                                                                       |
| ALT                                | alanine aminotransferase                                                                                                                                                                                                                                                                                                                                                                                                                                                                                                                                                                                                                                                                   |

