### 9.5.5 Electrocardiogram (ECG)

ECGs will be performed for safety monitoring purposes only and will not be presented. Any clinically significant findings from ECGs will be reported as an AE.

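### The protocol's instruction for recording ECG findings as adverse events is narrower than the rule the SAP relies on, so significant ECG changes without a diagnosis have no assured route into the ECG part of the primary endpoint

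*Combined protocol and SAP*

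**What the plan says.** Table GZEA.1 has two primary endpoint bullets. The first is the incidence of AEs and SAEs. The second is "Clinically significant changes in vital signs, safety laboratory parameters, and ECGs". ECG change is thus one of three items in the second bullet, listed apart from AE incidence.

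For sites, protocol section 9.4.4 gives two instructions on significant ECG findings:

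- AE reporting through the eCRF applies to "Any clinically significant findings from ECGs that result in a diagnosis and that occur after the subject receives the first dose".
- The next paragraph begins "If a clinically significant finding is identified (including, but not limited to, changes in QT/QT interval corrected for heart rate [QTc] interval from baseline". It calls for a decision on whether the subject continues, a decision on subject management, and documented review of the printed tracing. It says nothing about AE reporting.

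For analysis, protocol section 10.3.1.2 states: "Safety parameters that will be assessed include safety laboratory parameters, vital signs, and ECG parameters". It continues: "The parameters will be listed and summarized using standard descriptive statistics".

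SAP section 9.5.5 states: "ECGs will be performed for safety monitoring purposes only and will not be presented". It then relies on the AE route: "Any clinically significant findings from ECGs will be reported as an AE". SAP section 3 gives the SAP precedence over the protocol's statistical section and undertakes to identify substantial differences. SAP section 11 identifies none.

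**The concern.** Once the SAP presents no ECG data of its own, AE records become the only output it names for the ECG component of a primary endpoint. What is reported then depends on how the AE instruction is worded, and the two documents word it differently. The SAP takes every significant finding to be an AE. The site instruction expressly covers only the subset that leads to a diagnosis.

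At stake is whether a significant but undiagnosed conduction or QT/QTc change appears in the report at all, and whether that depends on which site saw it. The component was meant to add information to AE incidence. As planned, it adds none beyond what sites choose to enter as AEs.

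**Working it through.** The plan gives no figure on this point, so the check is mainly a comparison of text.

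**Step 1. Do the two AE rules differ?**

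| Source | Findings to be reported as AEs |
|---|---|
| Protocol 9.4.4 | Clinically significant, and leading to a diagnosis, and after first dose |
| SAP 9.5.5 | Clinically significant, with no further condition |

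The protocol's set lies inside the SAP's set. They differ by the post-dose findings that are significant but undiagnosed.

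**Step 2. Does the protocol recognise findings in that difference?** Yes. The second paragraph quoted from 9.4.4 names QT/QTc change from baseline as an example of a significant finding and attaches no diagnosis to it.

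**Step 3. Is there another reporting route?** Protocol 10.3.1.2 provided one, since ECG parameters were to be listed and summarised. SAP 9.5.5 removes it and SAP 11 does not record the removal. SAP 9.1 promises listings of all databased data, which conflicts with 9.5.5 and leaves the position unclear. Interval listings would in any case show measured values. They would not show the investigator's judgement of clinical significance, which is what the endpoint refers to.

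**Step 4. Which findings are exposed?** Heart rate is covered elsewhere. SAP 9.5.4 summarises AOBPM pulse rate by treatment and timepoint, compares each dose with placebo in a repeated-measures model, and relates heart rate to concentration. The exposed findings are therefore mainly rhythm, conduction and interval changes.

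**Step 5. How sensitive is the result to one case?**

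- The Schedule of Activities has six scheduled post-dose ECGs: 6 h, 12 h, and Days 2, 8, 29 and 85.
- Protocol 5.2 targets 48 evaluable subjects, 36 of them active, over six cohorts.
- Scheduled post-dose ECGs at that target: 6 × 48 = 288.
- Active subjects per dose: 36 / 6 = 6.
- One case recorded or missed in a dose group: 1/6 − 0/6 = 16.7 percentage points.

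These figures apply at the evaluable target. Up to 70 subjects may be enrolled, Cohort 4 is being repeated (Appendix 6), and the safety population is everyone dosed. The number of ECGs can therefore reach 6 × 70 = 420, and a dose group can exceed six.

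**The case against.** The strongest reply is that nothing is actually excluded. Section 9.4.4 does not say that undiagnosed findings are not AEs. Appendix 1 defines the term broadly: "An AE can therefore be any unfavorable and unintended sign (including an abnormal laboratory finding), symptom, or disease temporally associated". Section 9.2 has sites record any AE and alert the sponsor to anything unusual. A careful investigator could enter an undiagnosed QTc change as an AE and comply with every section. This stands. A reader might infer that the protocol bars such findings from AE reporting, or that they necessarily drop out of the endpoint, and the text supports neither reading. What remains is that a specific ECG instruction and a general definition point different ways, so practice can reasonably vary between sites.

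The second reply is that the tracings are not lost. All digital ECGs from Day 1 go to a central laboratory database, may be overread, and machine-read intervals may be used in reporting. This also stands as to the raw data. It does not supply the investigator's significance judgement, and the SAP as written does not use the data. The eCRF is not among the documents, so whether that judgement is captured in another field cannot be checked.

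A reader might also link the gap to the only anticipated risk, the heart-rate decrease seen in monkeys. That link is weak. Protocol section 3.3 says the decrease came without AEs and also without significant ECG findings, and heart rate is analysed through AOBPM whatever happens to the ECGs.

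Finally, the 17 points would apply to any missed event in any group of six. They do not measure how often a finding is significant but undiagnosed.

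**Conclusion.** The mismatch is real and worth correcting, but modest. The protocol's express ECG-to-AE instruction is narrower than the one SAP 9.5.5 depends on. The SAP has also removed the protocol's ECG listing and summary without declaring it. Together these leave significant but undiagnosed post-dose ECG changes without an assured route into the reported ECG component of the primary endpoint.

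The conclusion is that such findings can go unreported and that sites may differ. It is not that they will be missed or that incidence is known to be under-counted. The frequency cannot be estimated from the documents. The only size available is the sensitivity to one case, 17 percentage points in a dose group of six, which assumes the 48-subject target split evenly over six cohorts. The conclusion also assumes that no eCRF field outside the AE page records the significance judgement.

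**What to change.** 1. In protocol 9.4.4, delete the condition that the finding must lead to a diagnosis. Every clinically significant ECG finding after dosing is then entered as an AE, as SAP 9.5.5 assumes. Carry the same wording into the eCRF completion instructions.
2. In the SAP, report by treatment the number of subjects with at least one clinically significant post-dose ECG finding. This gives the ECG component its own result.
3. Reconcile SAP 9.5.5 with protocol 10.3.1.2. Either restore the listing and descriptive summary of ECG parameters, or keep the omission and record it in SAP section 11.

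The cost is one deleted condition, one added table and a section 11 entry or a restored summary. No procedure is added. There will be a few more AE entries, and the stated AE incidence may rise slightly. The documents define neither clinical significance nor diagnosis, so investigator judgement remains. The change removes the conflict between the two rules but not all variation between sites.
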